**Figure 1 F1:**
[figure not shown]
Protocol of evaluation and intervention for reduction of cardiovascular risk factors.

### Instruments

2.7

The main instrument is the HRV that will be evaluated in 2 ways: at rest and in exercise. At rest, to describe the autonomic profile of diabetic and exercise patients for 2 moments (pre- and postintervention) to observe the response to the stimuli offered to the patient during the stages (warm up—5 minutes, aerobic training—30 minutes, strength training—20 minutes, cool down—5 minutes) of metabolic rehabilitation.

In the first form of collection (at rest) patients will be placed in the supine position, where they will remain for 20 minutes in an air-conditioned room (22–25°), with a capture tape attached at the time of the xiphoid process. Such a brace has 2 electrodes attached to a sealed electronic transmitter, which pick up the heart's electrical impulses to which it is transmitted to the POLAR^[18]^ heart rate monitor attached to the volunteer's wrist.

In the second form of collection (in exercise), patients will undergo a metabolic rehabilitation program, however, previously they will also position the brace at the level of the xiphoid process to record the data and then initiate the intervention. This equipment will be positioned in the patient from the beginning of the metabolic rehabilitation and will remain until the end of the recovery.

The HRV will be analyzed by means of linear methods, analyzed in the domains of time and frequency, and also by nonlinear methods and the Poincaré plot.^[19]^

The analysis of the HRV will be performed from the heart beat recorded to beat throughout the protocol, and only series with more than 95% of sinus beats will be used for analysis.^[20]^

After the error check, the trace will be selected for analysis and subjected to a digital filtering, performed in Polar Precision Performance SW software (version 4.01.029). Finally, the HRV analysis will be done using the software: Kubios.^[15]^

Another instrument used is the 6MWT, which aims to evaluate an individual's response to exercise and provides an overall analysis of the respiratory, cardiac, and metabolic systems.^[21]^ The test consisted of a walk at maximum speed and constant (without running) in a corridor of 30 m, free of human traffic and marked to each meter by yellow tape, the delimitation of the circuit was indicated by signaling cones during the test was used verbal stimuli every minute, so that the participant did not reduce the speed of the walk as: “You are walking very well, continue like this!,” “Keep up the pace,”^[22]^ and at the end, the distance traveled (DT) in meters is compared with the predicted DT that is calculated by means of the formula that indicates the distance expected for the Brazilian population: 6MWT distance (meters) = 622,461 − (1846 × age in years) + (61,503 × male = 1, female = 0).^[23]^

Still, 2 questionnaires will be applied, one that evaluates quality of life and another that evaluates the quality of sleep of the patients. The quality of life questionnaire should be specific for the metabolic alteration present, and for this study the DQOL, which is a specific instrument to measure the quality of life of patients with T2DM, will be applied. This questionnaire has 44 separate questions in 4 domains: satisfaction with 15 questions, impact with 18 questions, social/vocational concerns with 7 questions and concerns related to diabetes with 4 questions. The answers are systematized on a 5-point scale. In an intensity scale is satisfaction (1 = very satisfied, 2 = very satisfied, 3 = average satisfied, 4 = not very satisfied, 5 = not satisfied). In frequency scale are impact and concerns (1 = never, 2 = almost never, 3 = sometimes, 4 = almost always, 5 = always). The result established in these scales for better quality of life values closer to 1.^[24]^

Finally, the quality of sleep of these patients will be evaluated through the Pittsburgh Sleep Quality Index Questionnaire (PSQI) developed by Buysse.^[25]^ This instrument has 19 questions of self-report, 5 questions directed to the spouse or companion, and 5 questions that are used only for clinical practice. The 19 questions are categorized into 7 components, graded in scores of 0 (no difficulty) to 3 (severe difficulty). The 7 components are: C1 subjective sleep quality, C2 sleep latency, C3 sleep duration, C4 usual sleep efficiency, C5 sleep disturbances, C6 sleep medication used, and C7 daytime sleep dysfunction.^[26]^

The sum of the values attributed to the 7 components ranges from 0 to 21 in the total questionnaire score indicating that the higher the number the worse the quality of sleep. A total score greater than 5 indicates that the individual is experiencing major dysfunctions in at least 2 components, or moderate dysfunction in at least 3 components.^[26]^

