### Data analysis

4.3

Data will be expressed as mean and standard deviation. The SPSS software version 24.0 will be used for statistics. The descriptive data will be measured by measures of central tendency and dispersion. The Shapiro–Wilk test will be used to verify the normality of the data. To compare the cardiorespiratory parameters, we will use the Friedmann test or the ANOVA test of repeated measures according to the normality of the data. The level of significance will be *P* < .05. All values will be compared with the rest condition.

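### Planned HRV tests need every series from a patient, so one series rejected by the 95% sinus-beat rule discards that patient's other valid series; a mixed model would keep them

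*Protocol article*

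**What the plan says.** Section 2.6 of the protocol article names HRV as an outcome variable, collected before and after the programme. Section 2.7 describes the recordings: "The main instrument is the HRV that will be evaluated in 2 ways: at rest and in exercise". The exercise recording spans four stages (warm-up, aerobic, strength, cool-down) and is made at two moments, pre- and postintervention. The quality filter works on series: "only series with more than 95% of sinus beats will be used for analysis".

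Section 4.3 fixes the analysis. "The Shapiro–Wilk test will be used to verify the normality of the data", and on that basis "we will use the Friedmann test or the ANOVA test of repeated measures according to the normality of the data". It adds that "All values will be compared with the rest condition", and that SPSS 24.0 is the software. It speaks of cardiorespiratory parameters and does not name HRV. I take HRV to be covered, because a rest condition followed by exercise stages is the natural subject of these tests.

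No target sample size is given. Section 4.1 reports 9 patients treated by the end of June 2017, with recruitment continuing.

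**The concern.** The filter removes single series, but the planned tests work on whole patients. Classical repeated-measures ANOVA and Friedman both need a complete row for each patient. A patient with one rejected recording therefore leaves the comparison, along with all the recordings that passed. The set analysed becomes smaller, and it is selected for clean signals throughout. Because everything is compared with rest, a failed rest series also removes the reference.

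Two further weaknesses come from choosing the test by Shapiro–Wilk:

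- Section 2.7 plans time-domain, frequency-domain, nonlinear and Poincaré indices. At small numbers, closely related indices may be sent to different tests by chance.
- The two branches do not answer the same question. Section 2.7 sets out to observe the response to the exercise stages before and after the programme, which is a time by stage interaction. Repeated-measures ANOVA can test it. Friedman, a one-way test, applied to the recorded values cannot.

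**Working it through.** The article states no series-failure rate, SD, effect size or target N, so there is no figure of its own to reproduce. The checks below show consequences under stated assumptions.

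**Inputs.** From section 2.7: rest plus four stages, two moments, and the series-level filter. From section 4.3: the two tests and the gate. From section 4.1: 9 patients so far. Assumed: a failure rate q of 5% or 10% per series, with independent failures.

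**Block size k.** The article does not fix what counts as a series or a block. Three readings fit:

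- k = 4: one trace for rest and one for exercise, at each of two occasions (2 × 2).
- k = 5: rest plus four stages within one occasion (1 + 4).
- k = 10: both occasions in one block (2 × 5).

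**Complete patients.** The share complete is (1 − q)^k. The share of all series that are valid is 1 − q, so the share valid but unused is (1 − q) − (1 − q)^k.

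| k | q | Complete patients | Expected out of 9 | Valid series unused |
|---|---|---|---|---|
| 4 | 5% | 0.95^4 = 81.5% | 7.3 | 95.0 − 81.5 = 13.5% |
| 4 | 10% | 0.90^4 = 65.6% | 5.9 | 90.0 − 65.6 = 24.4% |
| 5 | 5% | 0.95^5 = 77.4% | 7.0 | 95.0 − 77.4 = 17.6% |
| 5 | 10% | 0.90^5 = 59.0% | 5.3 | 90.0 − 59.0 = 31.0% |
| 10 | 5% | 0.95^10 = 59.9% | 5.4 | 95.0 − 59.9 = 35.1% |
| 10 | 10% | 0.90^10 = 34.9% | 3.1 | 90.0 − 34.9 = 55.1% |

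With 9 patients, k = 5 and q = 5%, the chance of losing at least one patient is 1 − 0.774^9 = 90%.

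Independence is the pessimistic end. If failures were wholly clustered, so that a patient fails on every series or on none, complete patients would be 1 − q (95% or 90%) for any k, and no valid series would be wasted. The truth lies between.

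**Normality gate, one test on one set of values.** Simulated Shapiro–Wilk rejection rates at 0.05, 5,000 samples per entry:

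| Distribution | n = 9 | n = 20 | n = 30 |
|---|---|---|---|
| Log-normal, log-SD 0.5 | 22% | 52% | 73% |
| Exponential | 38% | 82% | 97% |
| Log-normal, log-SD 1 | 56% | 93% | 99% |

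The gate also errs the other way. On normal data, 5 independent pre-tests give at least one rejection with probability 1 − 0.95^5 = 22.6%; for 10 it is 1 − 0.95^10 = 40.1%.

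**Type I error of the two-step choice.** I simulated five conditions with equal correlation 0.5 on the underlying normal scale, taking Friedman if any condition failed Shapiro–Wilk and ANOVA otherwise (4,000 runs; normal and log-normal data). The error was 4.7% to 5.2% at n = 9 and 4.2% to 5.1% at n = 20. There is no material inflation.

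**The case against.** The best case for the plan is that it never says whole patients are dropped. It excludes series, and how a patient with a gap is handled is the sort of detail a condensed article leaves to a fuller document. That is fair as far as it goes. But the tests are stated, and needing complete rows is a property of those tests, so the loss follows unless another method is added.

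Several stronger readings are tempting, and the documents do not support them:

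- **All of the patient's data are lost.** Only the HRV comparison concerned is affected. Glycated hemoglobin, walk distance and the questionnaires do not pass through the sinus-beat rule.
- **Ten series per patient is the only block size.** The comparison with rest fits five conditions within an occasion equally well. The belt stays on throughout the session, so one exercise trace per occasion is also possible.
- **The normality test is underpowered without qualification.** Nine is accrual to date. At 30 or more patients, power against clear skewness is good.
- **The gate inflates false positives.** It did not in the cases simulated.
- **Means and SDs are reported whichever test is used.** Section 4.3 does say "Data will be expressed as mean and standard deviation", but it also plans measures of central tendency and dispersion in general, which leaves room for medians.

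It is plausible that rejections cluster in the stages with movement or in patients with ectopic beats, but the article gives no figure for this. Section 2.2 excludes several rhythm disorders and antiarrhythmic users, and section 2.7 adds an error check and digital filtering. These should lower the failure rate by an unknown amount. The 95% filter itself is a reasonable signal-quality rule and is not the fault.

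**Conclusion.** The point holds for the HRV comparisons. Pairing a series-level filter with tests that need complete patients wastes valid recordings. At an assumed independent failure rate of 5% to 10% per series, complete patients fall to between 81% and 66% for 4 series, 77% and 59% for 5, and 60% and 35% for 10. The loss is smaller where failures cluster within patients. The failure rates and the block sizes are my assumptions.

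The objection to the gate is narrower. At the 9 patients accrued so far, a single Shapiro–Wilk test detects clear skewness in roughly 20% to 55% of samples, so the test given to each index is partly a matter of chance. This fades as numbers grow, and error control is not harmed. The inability of the Friedman branch to test time by stage does not depend on sample size.

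This is an inexpensive improvement to the analysis, not a flaw that invalidates the trial.

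**What to change.** Change section 4.3 and leave the filter in section 2.7 as it is, at series level.

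- Analyse each HRV index with one prespecified linear mixed model: time, stage (with rest as the reference level) and time by stage as fixed effects; random effects for patient and for occasion within patient; small-sample degrees of freedom (Satterthwaite). Use every valid series. The occasion term is needed because a patient effect alone ignores the correlation among recordings from the same session. The MIXED procedure in SPSS 24 can fit this, and comparisons with rest become contrasts in the model.
- Use the log scale for indices that are positive and skewed, and list those indices before the data are analysed.
- Drop the Shapiro–Wilk gate. Keep the rank tests as a sensitivity analysis.
- Report the number of valid series by stage and occasion.

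The cost is revised analysis wording, slightly more programming, and results given as ratios for log-scaled indices. The model recovers the valid series that complete-patient tests discard. It reduces selection bias but does not remove it if rejection depends on the HRV values that were not observed, which is why the counts of valid series should be shown.

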## Material

3

For General Cardiovascular Semiology you will need a stethoscope, sphygmomanometer, stopwatch, and thermometer.

The equipment that will be used is the Polar RS800CX heart rate receiver (RR) for the capture of the RR intervals, previously validated equipment to capture the HR beat and use of its stored data for future HRV.^[18]^ This equipment consists of 2 electrodes mounted on a sealed electronic transmitter that will be positioned in the volunteer's chest at the level of the distal third of the sternum, using an elastic band. These telemetric units will obtain the electrical impulses of the heart and will transmit such information through an electromagnetic field to the monitor that will be positioned in the wrist.^[19]^

For the 6MWT you will need a pulse meter and pulse oximeter, both handheld, stopwatch, measuring tape, signaling cones, stethoscope, sphygmomanometer, symptom perception scale printed on plasticized paperboard, suitable size and allowing easy reading and chair along if the patient needs rest.

After conducting the evaluation, equipment will be needed for the implementation of the metabolic rehabilitation program. The necessary equipments are: treadmill, cardiofrequencimeter (to monitor the training), dumbbells and shiners of the most diverse loads to respect the result of the test of a maximum repetition of each individual.

## Measures

4

### Primary outcomes

4.1

Recruitment began in September 2016, and is underway. A total of 9 patients were evaluated and submitted to the intervention protocol by the end of June 2017.

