### Data collection

2.6

The evaluation instrument of the research will be applied before and after the practice of the proposed rehabilitation program. The instrument is based on the following collection protocol: BP, HR, Borg scale, respiratory rate, oxygen saturation, distance walked through the 6-minute walk test (6MWT), quality questionnaire (Which must be specific for each disease, and therefore the research used the diabetes quality of life-Brazil-DQOL), sleep quality questionnaire (Pittsburgh) and also the outcome variables that are glycated hemoglobin (sent by physician along with medical referral) and HRV through the cardiofrequency meter.

It is also suggested the insertion of cardiovascular and metabolic serum markers of individuals submitted to a metabolic rehabilitation program, in order to evaluate patients regarding cardiovascular risks.

With this evaluation, before and after the rehabilitation program, it will be possible to observe the response of these variables (Fig. 1).

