### Secondary outcomes

4.2

The protocol may provide subsidy for implantation of metabolic rehabilitation programs in patients with other CVD such as dyslipidemia, hypertension among others.

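### Sections 4.1 and 4.2 name no measured outcome, and HbA1c and an unspecified HRV measure are left unranked, so the article does not say which result is confirmatory

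*Protocol article*

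**What the plan says.** Section 4.1, Primary outcomes, consists of two sentences: "Recruitment began in September 2016, and is underway" and "A total of 9 patients were evaluated and submitted to the intervention protocol by the end of June 2017". Section 4.2, Secondary outcomes, consists of one: "The protocol may provide subsidy for implantation of metabolic rehabilitation programs in patients with other CVD such as dyslipidemia, hypertension among others".

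Section 2.6, Data collection, lists the assessments made before and after the programme and sets two of them apart as "the outcome variables that are glycated hemoglobin (sent by physician along with medical referral) and HRV through the cardiofrequency meter". Section 2.7, Instruments, treats HRV as the main instrument, recorded at rest and in exercise, and states: "The HRV will be analyzed by means of linear methods, analyzed in the domains of time and frequency, and also by nonlinear methods".

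Section 4.3, Data analysis, gives one level for everything: "The level of significance will be *P* < .05". It assigns its tests to one group of variables: "To compare the cardiorespiratory parameters, we will use the Friedmann test or the ANOVA test of repeated measures according to the normality of the data". It closes with "All values will be compared with the rest condition".

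**The concern.** The two sections that should say what the trial is judged on contain other material: study status in one, a possible future application in the other. This is more than detail left to a statistical analysis plan. The article has dedicated sections for these items and fills them with the wrong content.

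A 5% level protects a trial's conclusion only if it is known in advance which comparison carries that conclusion. Here a reader of the final report could not check, from this article, whether the result put forward as the main one was the planned one. HRV makes this harder, because it is not a single variable: a choice of index, of condition (rest or an exercise stage) and of contrast is still open.

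**Working it through.** **Step 1. Does any other section settle the primary outcome?** The article describes its target in five places:

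- Abstract, Method: the haemodynamic and glycaemic response.
- Section 2, Method: the autonomic response together with cardiovascular and metabolic serum markers (section 2.6 only suggests adding such markers).
- Section 2.6: HbA1c and HRV as the outcome variables.
- Section 2.7: HRV as the main instrument.
- Section 5: a registered title naming cardiorespiratory parameters and glycated haemoglobin.

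These differ, and none uses the word primary for a variable. The closing sentence of 4.3 does not settle it either: a comparison with rest cannot apply to HbA1c or to the two questionnaires.

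**Step 2. Count the candidates.**

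- Outcome variables named in 2.6: HbA1c and HRV, so k = 2 if HRV is reduced to one index.
- All measures listed in 2.6: BP, HR, Borg, respiratory rate, oxygen saturation, 6MWT distance, DQOL, PSQI, HbA1c, HRV, so k = 10.
- The same list with HRV taken as one index from each of the time, frequency and nonlinear domains: 9 + 3, so k = 12.

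Serum markers, the four DQOL domains, and systolic and diastolic pressure counted separately would add to this.

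**Step 3. Chance of at least one false positive.** The article states no family-wise figure, so there is none to reproduce. With each test at 0.05 and independent tests, the chance is 1 − (1 − 0.05)^k:

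- k = 2: 1 − 0.95² = 0.0975, or 9.8%
- k = 10: 1 − 0.95¹⁰ = 0.401, or 40.1%
- k = 12: 1 − 0.95¹² = 0.460, or 46.0%

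**Step 4. Allow for correlation.** The measures are taken on the same patients, so independence is the unfavourable end. The article gives no correlations. The values below assume a common correlation and two-sided tests, with 400,000 simulated sets of normal statistics:

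| k | 0 | 0.3 | 0.5 | 0.8 |
|---|---|---|---|---|
| 2 | 9.8% | 9.5% | 9.1% | 7.9% |
| 10 | 40.1% | 35.1% | 28.8% | 17.4% |
| 12 | 46.0% | 39.6% | 32.0% | 18.6% |

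Every entry exceeds 5%.

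**Step 5. After the fix.** One named primary variable with one contrast, tested at 0.05, has an error of 0.05. Two co-primaries at 0.05/2 = 0.025 each keep the total at or below 0.05; Holm does the same with somewhat more power.

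**The case against.** The strongest case on the other side is that the article contains a partial hierarchy. Section 2.6 separates HbA1c and HRV from the other assessments, 2.7 gives HRV the leading place, and the registered title names glycated haemoglobin. So Borg or oxygen saturation does not stand level with HbA1c. That is fair, and it narrows the field to two. It does not rank the two, and one of them is still a family of indices.

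A multiplicity procedure may also sit in a statistical analysis plan that is not shown, and the registry entry may name a primary outcome. Both are possible. Neither puts an outcome into 4.1 or 4.2.

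Four stronger readings are tempting, and the document does not support them:

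- A reader might infer that a dozen measures will each be tested at 0.05. Section 4.3 assigns its tests only to the cardiorespiratory parameters and names none for HbA1c, DQOL or PSQI. Testing everything is an inference from the single significance level, and reaching 12 requires splitting HRV.
- A reader might count every exercise stage against rest: 3 indices × 4 stages × 2 moments = 24 further tests, 36 in all, and 1 − 0.95³⁶ = 84%. The named tests are omnibus tests. One per index per moment adds 3 × 2 = 6, giving 18 tests and 1 − 0.95¹⁸ = 60% under independence. Whether any follow-up contrasts are adjusted is not stated.
- A reader might infer that the outcome is being chosen after looking at data. The article says that 9 patients were evaluated and treated; it reports no analysis of their results.
- A reader might take 4.2 as claiming a result in other diseases. It speaks only of a possibility, and section 2.2 does not exclude hypertension or dyslipidaemia. It is misplaced text.

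**Conclusion.** The point holds as a failure to designate outcomes. Sections 4.1 and 4.2 name no measured variable, and no other section ranks HbA1c against HRV or fixes an HRV index, condition or contrast. The confirmatory result therefore cannot be identified from this article.

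The best-supported size is the smallest: up to 9.8% for the two named outcome variables, if HRV is reduced to one index and neither test is adjusted. The range of 40% to 46% for 10 to 12 tests is conditional on all measures being tested and on independence; for 12 tests it falls to about 19% to 40% at assumed correlations of 0.8 to 0.3. The finding does not depend on these larger figures, nor on any suggestion that results have already been examined. It should be corrected before the trial is analysed.

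**What to change.** Replace the text of 4.1 with one primary variable, either HbA1c or one specified resting HRV index, and give its time point and contrast. Alternatively, name both as co-primaries with a multiplicity adjustment such as Holm. Section 2 calls the trial randomised. If there is a randomised comparator, the contrast must be the between-arm difference at the end of the programme, adjusted for baseline. If there is not, describe the contrast as a pre-post change. If the registry entry already names a primary outcome, state that one or explain the difference.

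List the other measured variables in 4.2 as secondary or exploratory, reported as estimates with 95% confidence intervals. Move the recruitment text to a study-status paragraph and the other-disease text to the Discussion.

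State that registration (March 2017) followed the start of recruitment (September 2016), and whether the primary outcome was chosen without sight of results from the 9 patients treated by the end of June 2017.

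The cost is protocol wording and, where needed, a registry update. The downside is that most measures become exploratory and can no longer carry the trial's conclusion.
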